## Abstract

**Background:**

Anorexia nervosa (AN) has amongst the highest mortality rates and the highest treatment costs of any psychiatric disorder. Recently, interest in non-invasive brain stimulation as a novel treatment for AN has grown. These include repetitive transcranial magnetic stimulation (rTMS) and transcranial direct current stimulation (tDCS).

**Methods:**

This double-blind, randomised sham-controlled trial will compare the relative acceptability and efficacy of tDCS and rTMS in people with AN. 70 participants will be randomised to active or sham tDCS, or active or sham rTMS treatment (2:1:2:1 ratio) over an 8-week treatment period. Participants will receive treatment as usual across the study duration. The primary outcomes are change on the Eating Disorder Examination Questionnaire and treatment acceptability. Secondary outcomes will include change in weight, cognition, mood, interpersonal functioning, and quality of life. Following the 8-week assessment, all participants will have the option of receiving an additional 12 weeks of at-home tDCS. A follow-up assessment will be conducted at 20 weeks post treatment.

**Discussion:**

Research into non-invasive brain stimulation as treatments for AN has potential to improve clinical outcomes for patients by comparing the relative efficacy and acceptability of both treatment modalities in the inpatient and at-home setting (i.e., for at-home tDCS) results from this study will provide important information for informing future larger clinical trials of these treatments for AN.

***Trial registration*:**

ClinicalTrials.gov Identifier: NCT05788042.

## Background

Anorexia nervosa (AN) is a life-threatening eating disorder characterised by a restriction of energy intake relative to needs leading to a significantly low weight [4]. Lifetime prevalence rates are up to 4% among females and 0.3% among males [73], with age of onset predominantly in adolescence [48]. AN has amongst the highest mortality rate of any psychiatric disorder [5]. Complications from malnutrition affect all body systems [31] including growth retardation, osteoporosis, infertility and changes in brain structure [43]. AN is also associated with psychological complications including mood disorders, anxiety disorders, obsessive compulsive disorder, substance abuse, and personality disorders [37, 56]. Moreover, individuals with AN exhibit cognitive impairment, with severity correlating with degree of malnutrition and chronicity [34]. Although, specialised family-based psychology treatments are beneficial for adolescents [17, 32, 51]; psychotherapy and pharmacotherapy interventions for adults with AN, have limited efficacy with reports of 70–90% of patients not achieving full remission [12, 24, 25, 39, 68, 69, 77] with no significant advantages of combining these treatments [6, 10, 74]. The investigation of novel treatment strategies is thus critical.

Recently, interest in the therapeutic potential of non-invasive brain stimulation as a novel treatment for AN has grown. Preliminary evidence has suggested that both transcranial direct current stimulation (tDCS) and repetitive transcranial magnetic stimulation (rTMS) targeting the dorsolateral prefrontal cortex (DLPFC) can reduce core eating disorder symptoms in AN [29].

### Transcranial direct current stimulation (tDCS) for people with AN

Transcranial direct current stimulation (tDCS) is a safe, non-invasive brain stimulation technique that involves the passing of a weak direct electrical current (typically 1–2 mA) through the cerebral cortex via electrodes placed upon the scalp. Animal and human studies have shown that tDCS changes the excitability of neurons in stimulated regions in a polarity dependent manner, causing changes in spontaneous neural activity that outlast the period of stimulation [50]. Meta-analyses of randomised controlled trials (RCTs) have demonstrated significant therapeutic benefit in depression [63] and acute cognitive enhancing effects in healthy and clinical samples [8, 26]. tDCS has relative advantages compared to other non-invasive brain stimulation methods, including reduced costs for equipment and the ability for remotely supervised at-home treatment using protocols developed by our team [3]. To date, one double blind RCT [7] has examined the therapeutic potential of tDCS in AN. In this study 43 participants with AN were randomly assigned to receive active or sham tDCS over the left DLPFC over ten 30-min sessions. Although the results did not show major improvements in AN psychopathology or weight recovery compared with sham tDCS, active tDCS reduced the need for excessive control over food intake and improved body image. In addition, three small open-label studies [16, 45, 71] and one case report [67] have examined tDCS efficacy of left DLPFC anodal stimulation in people with AN. Although these studies have varied in terms of treatment protocols (e.g., treatment administered three times a week over 6 weeks or once and twice per day over ten days), all studies suggested benefits for core eating disorder symptoms with the pilot studies showing maintained benefits at 1 month follow up post end acute treatment. Although preliminary, these studies have suggested that anodal tDCS targeting the left DLPFC may be beneficial for improving AN symptoms, though larger RCTs are required.

### Repetitive transcranial magnetic stimulation (rTMS) for people with AN

Repetitive transcranial magnetic stimulation (rTMS) involves the repeated application of a strong, highly localised magnetic field to a small cortical area, depolarising neurons in the stimulated target area and producing downstream neuromodulatory effects [46]. The most studied psychiatric application of rTMS has been for depression that is treatment-resistant, or difficult-to-treat [59]. In 2008, rTMS gained US FDA clearance for treatment-resistant depression. Other psychiatric and neurological disorders approved and treated with rTMS in other jurisdictions include obsessive compulsive disorder, refractory schizophrenia, and Alzheimer's disease. rTMS treatment may also have cognitive enhancing effects. A systematic review and meta-analysis of rTMS cognitive effects in depression found significant cognitive enhancement compared to sham treatment [55].

To date, one double-blind sham-controlled RCT [20, 21] has examined the effects of rTMS in people with severe enduring AN (i.e., illness duration ≥ 3 years). In that study, 34 patients were randomly assigned to receive active or sham rTMS administered to the left DLPFC over 20 consecutive weekdays. Results showed that rTMS was safe and well tolerated. Importantly, clinical benefits with active rTMS were observed, with moderate to large sized improvements for psychological symptoms (anxiety and depression) and medium sized improvement in quality of life at a 3 month follow up. Moreover, an open 18 months follow up showed further improvement in eating disorder symptoms and maintained effects on mood [22]. Several open label studies [23, 28, 47, 58, 76] and case studies [14, 27, 41, 57] have also observed promising therapeutic effects with AN symptoms, with the majority of studies targeting the left DLPFC. Three pilot studies though have explored the efficacy of alternative treatment targets, the dorsomedial prefrontal cortex (DMPFC; Dunlop et al. [28]; Woodside et al. [76]) and the insula [47] with similar promising therapeutic effects for core AN symptoms. Interestingly, a recent secondary analysis of a feasibility study which involved 26 participants with AN who received 20 rTMS treatments targeting the left DLPFC over four weeks found preliminary evidence of greater improvement in core AN symptoms at 3 month follow up in the participants who took concurrent antidepressant medications [23]. In the one trial which examined longer-term outcomes, McClelland et al. [58] found that 3/5 patients had sustained clinical benefits for core AN symptoms (i.e., reduced urge to restrict food intake and the feeling of being full or fat) following a 4-week treatment course at a 12-month follow up. Taken together these studies indicate that that rTMS is safe and well tolerated treatment for AN, however, further research is required to investigate optimal treatment protocols with larger RCTs also required to determine treatment efficacy.

### Current study

Despite initial promising findings, the potential therapeutic benefits of tDCS and rTMS treatment for AN remain unclear. To date, tDCS and rTMS studies have varied in terms of treatment protocols (e.g., administered once or twice per day, up to 20 treatment sessions) and indicated limited efficacy and acceptability of both treatments. Further no study has directly compared the efficacy and acceptability of tDCS and rTMS. Here we propose to conduct the first double-blinded, randomised sham-controlled study to directly compare the therapeutic efficacy and acceptability of these two novel treatment modalities. This study will extend findings from previous studies in several ways, including: (1) using self-administered instead of in-clinic administered tDCS which has potential advantages for people living remotely or with restricted access to health care services; (2) using a newer form of patterned rTMS (intermittent theta burst stimulation: iTBS) which is much quicker to administer than standard rTMS; (3) administering an increased number of treatments and longer sham-controlled treatment period (8 weeks) compared to the only prior RCT of rTMS in AN (20 treatments) and previous studies (up to 4 weeks of acute treatment only); (4) the option of longer-term continuation at-home tDCS treatment to examine the potential for longer-term clinical benefits; (5) exploring participants’ experience of treatment though qualitative interview; and (6) extending the field of treatment strategies for AN expected outcomes including data on the relative efficacy, acceptability and cost effectiveness for both treatment modalities in the inpatient and at-home setting (i.e., for at-home tDCS). This will be important for informing a future larger definitive multicentre clinical trial. This pilot study’s main primary hypotheses are that both active treatment arms will produce clinical improvement in eating disorder psychopathology (measured with Eating Disorder Examination Questionnaire; EDE-Q; Fairburn [30]) at the end of 8-week randomised controlled period and that both active treatments will have high acceptability (measured with number of completed sessions for active tDCS and active rTMS in the acute 8-week RCT period).

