## Methods

### Design

This double-blind, randomised, sham-controlled trial will compare rTMS and tDCS acceptability and clinical outcomes in patients with AN. This study protocol was prepared in accordance with the SPIRIT and CONSORT guidelines. Participants will be randomised to one of four groups (2:1:2:1 ratio): active or sham tDCS, or active or sham rTMS. The brain stimulation protocols involve 84 sessions of tDCS (active or sham) or 56 sessions of rTMS (active or sham) over an 8 week treatment period. Participants in all groups will also receive treatment as usual (TAU) across the study duration. Following the end of 8 week randomised controlled period assessment, participants in all groups will have the option of receiving an additional open label 12 weeks of at-home, remotely supervised tDCS. A follow up assessment will be conducted at 20 weeks post treatment. A flowchart of the study is shown in Fig. 1.

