#### Primary outcomes

The efficacy analysis will be completed for both the mITT and PP population. Descriptive statistics and graphical methods will be used to show variability in the data. The size of the treatment effect for EDE-Q Global scores will be the change in scores from pre-treatment to post 8 weeks treatment for both active treatment arms. The acceptability analysis will be completed in the mITT population. Descriptive statistics will report the number of completed active tDCS and active rTMS treatments in the 8 week randomised controlled period.

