#### Secondary outcomes

Analyses of secondary outcomes will be competed in the mITT population. The size of the treatment effect will be the difference in outcome data (BMI, questionnaires, neurocognitive outcomes) between the active and sham treatment arms for both tDCS and rTMS, respectively, at 4 weeks, 8 weeks, and 20 weeks post treatment. These effect sizes will control for pre-treatment scores. Descriptive statistics will be used to show remission rates for all treatment arms at post 8 weeks and 20 weeks post treatment. Generalised linear mixed models will be used to compare the treatment arms for mood and psychological symptom outcomes. Exploratory analyses will investigate associations between changes in mood and neurocognition with active tDCS and rTMS, and improvement in core eating disorder symptoms.

Generalised linear models will be used to compare cost and quality of life/utility values (from AQoL-4D) between treatments arms over the 8 week randomised treatment. Cost effectiveness analysis will compare the health outcomes and economic outcomes (costs of duration of inpatient stay and readmissions during the follow up period) associated with both treatment modalities.

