## Discussion

AN has limited treatment outcomes, and the highest treatment costs of any psychiatric disorder [35]. This study is designed to investigate and compare relative acceptability and efficacy of two non-invasive forms of brain stimulation: tDCS and rTMS, which haven shown a potential to reducing core ED symptoms in AN [29].

Currently, one randomised sham controlled clinical trial each investigating tDCS [7] and rTMS [20, 21] have indicated limited efficacy for core AN symptoms, with the tDCS study observing reduction in need for excessive control over food intake and improvement in body image and the rTMS study observing improvements in psychological symptoms (anxiety and depression) and in quality of life. In these studies, the overall number of treatment sessions has been limited (i.e., 10 tDCS, 20 rTMS) which contrasts with standard therapeutic treatment protocols for other indications, for example depression [63]. This study will directly compare the therapeutic efficacy and acceptability of both treatment modalities with an increased number of treatments (tDCS 84 and rTMS 56 sessions) over a longer sham-controlled treatment period (8 weeks).

When designing the study, the potential burden on participants was considered due to the inclusion of an increased number of treatments compared to prior studies and the longer sham-controlled period. To minimise this burden, it was first decided to schedule the treatments around the participants’ inpatient and outpatient program at the hospital to minimise travel burden. Second, we implemented an overall 2:1 active to sham randomisation so that participants are twice as likely to receive active treatment in the sham controlled RCT phase of the study. Another strategy was to provide all participants who complete the first 8 weeks RCT the option of receiving 12 weeks of open label active home based tDCS treatment, i.e. the study provided the option of extended active tDCS treatment to all participants.

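### The stated aim is to compare tDCS with rTMS, but the primary analysis gives no tDCS–rTMS estimate or interval for EDE-Q or acceptability

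*Protocol article*

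**What the plan says.** The comparative aim appears in four places in the protocol article.

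- Abstract, Methods: the trial "will compare the relative acceptability and efficacy of tDCS and rTMS in people with AN".
- Current study: the purpose is "to directly compare the therapeutic efficacy and acceptability of these two novel treatment modalities", put forward after noting that no earlier study has done so.
- Design: the trial "will compare rTMS and tDCS acceptability and clinical outcomes in patients with AN".
- Discussion: "This study will directly compare the therapeutic efficacy and acceptability of both treatment modalities".

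The primary hypotheses, also in Current study, are not comparative. They are that "both active treatment arms will produce clinical improvement in eating disorder psychopathology" by week 8, and that "both active treatments will have high acceptability".

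The primary analysis follows the hypotheses. Under Analysis, Primary outcomes, the EDE-Q Global treatment effect is the pre-to-post change over 8 weeks in each active arm. For acceptability, "Descriptive statistics will report the number of completed active tDCS and active rTMS treatments in the 8 week randomised controlled period". The outcome definitions earlier in the article agree with this.

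Under Analysis, Secondary outcomes, effect sizes are differences "between the active and sham treatment arms for both tDCS and rTMS, respectively". The same section plans mixed models comparing the arms on mood and psychological symptoms, generalised linear models comparing arms on cost and utility, and a cost-effectiveness comparison of the two modalities.

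**The concern.** The aim calls for a difference between two randomised arms. The analysis specified for the primary outcomes gives two separate within-arm summaries. Someone who follows the plan exactly will have an EDE-Q change for active tDCS, another for active rTMS, and no estimate of the difference or of its uncertainty. The comparison would then be made by eye, and a gap of half a standard deviation could be taken as real when the data are compatible with none.

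For acceptability there is a further difficulty. The measure is a count of completed sessions, and the two modalities schedule different numbers. Two counts side by side do not measure relative acceptability unless each is divided by what was scheduled.

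The article says the results will inform a larger trial. Relative efficacy and acceptability of the two modalities is part of what that trial would need, so the estimate should come with its imprecision visible.

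**Working it through.** **Which contrasts are planned, by outcome**

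| Outcome | Planned analysis | tDCS–rTMS difference specified? |
|---|---|---|
| EDE-Q Global, week 8 (primary) | Change within each active arm | No |
| Completed sessions (primary) | Descriptive count per active arm | No |
| BMI, questionnaires, neurocognition | Active versus sham within each modality | No |
| Mood, psychological symptoms | Mixed models comparing treatment arms | Arms compared |
| Cost, utility | Generalised linear models between arms | Arms compared |
| Cost-effectiveness | Comparison of both modalities | Yes |

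The mixed models do not reach the EDE-Q. Table 1 lists it under core AN symptoms, apart from mood (MADRS) and psychological symptoms (DASS-21). If the EDE-Q is counted among the questionnaires in the third row, its contrast is still active versus sham within a modality.

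**Scale of the acceptability measure**

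The scheduled totals follow from the Interventions section:

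- rTMS: 2 × 5 × 4 + 2 × 2 × 4 = 40 + 16 = 56
- tDCS: 2 × 7 × 4 + 1 × 7 × 4 = 56 + 28 = 84

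Both agree with the article. At the same 80% completion the counts are 0.8 × 84 = 67.2 and 0.8 × 56 = 44.8, a gap of 22.4 sessions with no difference in adherence. Conversely, 56 completed sessions are 100% of the rTMS course but 56/84 = 67% of the tDCS course.

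**Precision of the missing EDE-Q contrast**

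Inputs from the article: N = 70, allocation 2:1:2:1. Each active arm has 70 × 2/6 = 23.3 participants and each sham arm 70 × 1/6 = 11.7. The article gives no SD, so results are in units of the outcome's SD. Dropout of 20 to 30% is an assumption, as is a baseline correlation of 0.5 where it is used.

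Active tDCS minus active rTMS: half-width = t(0.975, 2n − 2) × √(2/n).

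| Dropout | n per active arm | √(2/n) | 95% CI half-width |
|---|---|---|---|
| 0% | 23.3 | 0.293 | 0.59 SD |
| 20% | 18.7 | 0.327 | 0.66 SD |
| 30% | 16.3 | 0.350 | 0.71 SD |

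Adjusting for a baseline that correlates 0.5 with the outcome multiplies these by √(1 − 0.5²) = 0.866, so 0.59 becomes about 0.51 SD.

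Sham-adjusted contrast, (active − sham tDCS) minus (active − sham rTMS), by normal approximation: 1.96 × √(2/23.33 + 2/11.67) = 1.96 × 0.507 = 0.99 SD with no dropout, and 1.19 SD at 30%.

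As a test, the active–active contrast with 23 per arm and two-sided 5% alpha (assumed) would have about 40% power for 0.5 SD and 77% for 0.8 SD. It is therefore suited to estimation, not to a formal test.

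**The case against.** The strongest reply is that the analysis matches the hypotheses. The article calls the study a pilot, its primary hypotheses are that each active arm improves and is acceptable, and the primary analysis addresses exactly those. That stands, and it is why no powered comparison is asked for. It does not remove the mismatch with an aim that the article states four times and presents as the novelty of the trial.

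A second reply is that a condensed article leaves contrasts and intervals to the full protocol or analysis plan. That is fair as to detail, and either document may contain the contrast. But the article is not merely silent: it defines the primary effect as within-arm change, and an analysis plan written from it would inherit the mismatch.

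Four stronger readings may tempt a reader, and the article does not support them.

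- *The trial cannot answer its comparative question.* Both active arms are randomised concurrently, so the design supports the contrast. Only the analysis as written omits it.
- *The plan infers a difference because one arm is significant and the other is not.* No significance test is planned for either primary outcome. Over-reading two separate results is a risk for readers, not a stated method.
- *No comparison across arms or modalities exists anywhere.* Such comparisons are planned for mood, psychological symptoms, cost, utility and cost-effectiveness. The gap is in the primary outcomes.
- *The double-blind claim fails altogether.* Participants will know their modality, since tDCS is self-administered, staff give rTMS, and no double dummy is described. This is a separate issue that bears on the self-reported EDE-Q. It does not extend to everyone blinded: the mood rater is asked to guess among all four arms and may be blind to modality.

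**Conclusion.** The point holds as a mismatch between the stated aim and the stated primary analysis. Followed as written, the plan yields no tDCS–rTMS estimate or interval on either primary outcome, and its acceptability counts cannot be compared directly (67.2 against 44.8 at equal 80% completion). It is not a fault in the randomisation, and the within-arm analysis is consistent with the pilot hypotheses.

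The missing EDE-Q contrast can be estimated only imprecisely: half-width about 0.59 SD with all 70 analysed, and 0.66 to 0.71 SD at 20 to 30% dropout. These figures are unadjusted and assume equal SDs and the target allocation. The session arithmetic rests only on the article's own schedule.

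**What to change.** Add the following to the primary analysis, labelled as estimation without a formal test.

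1. Active tDCS minus active rTMS in EDE-Q Global at week 8, adjusted for baseline, with a 95% CI.
2. The difference between active tDCS and active rTMS in percent of scheduled sessions completed (denominators 84 and 56), with a 95% CI. The per-protocol definition already uses a percentage of randomised treatments, so this scale is not new to the article.
3. A sentence, wherever the EDE-Q contrast is reported, that participants rate this outcome themselves and are not blinded to modality.

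The sham-adjusted difference of differences is optional; at a half-width of about 1 SD it would add little.

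If the investigators do not want a between-modality estimate, the alternative is to reword the aim in the four places so that it describes within-arm change and acceptability in each modality.

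Neither route changes the sample size, visits or data collected. The cost of the first is a wide published interval, which is an accurate picture of what a trial of this size can say about the two modalities.
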